### G2.2 Intention to treat analysis

The primary analysis of the clinical trial will be “intent to treat” (ITT) analysis based on the total cohort of randomized patients. This approach will be applied to the primary endpoint (live birth) as well as designated secondary endpoints. The difference between the incidence rates of live births for the two treatment groups will be examined by a two-sided test based on the standard Z-score (using the normal approximation to the binomial distribution). The common null hypothesis states that the effect of aspirin on the outcome is null compared to the placebo.

The secondary objectives (as described in Section A) with binary endpoints will be analyzed similarly as comparison of proportions. For binary outcomes such as pregnancy, the time to event may be of interest. In this case, survival analysis methods will be applied with the log-rank test for comparison of the two study treatment groups. For continuous outcome such as birthweight either parametric or non-parametric methods will be used as appropriate. If transformations to approximate a normal distribution are feasible, they will be carried out prior to the parametric analysis. The normality of the data will be examined both graphically using Q-Q plots and by formal tests (Wilks- Shapiro test). For data (either on original or transformed scale) assumed to be normally distributed the comparison of the two treatment groups will be carried out by a t-test. Alternatively if a non-parametric test is required, the Wilcoxon-Mann-Whitney test will be used.

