### **G.3 Interim analysis**

For a multi-year trial such as this one it is useful to examine the data as it accumulates in order to see if the study should be ended early or to catch any surprising developments. Such interim analysis needs to be planned formally. One of the most widely used procedures for interim analysis of a clinical trial is the  $\alpha$  spending function approach of Lan and DeMets. This method uses a function of time to specify the rate at which the total Type I error probability is to be spent during the trial interim looks so that this quantity does not exceed the desired overall Alpha level. For the EAGeR trial the spending function corresponding to the O'Brien-Fleming procedure will be used. The O'Brien- Fleming boundaries were chosen since for a given sample size they do not significantly change the overall power and are conservative early in the trial. By

conservative we mean that the proportions of success must be extremely different between the treatment arms to result in statistical significance early in the trial.

For our implementation the rate at which Type I error is spent is a function of elapsed time. We consider live birth as the primary trial endpoint and can expect events to start appearing approximately 10 months after subjects are randomized, that is month 16 of the trial. The accrual period will continue through month 40 while Phase II ends by month 57. Thus, for the interim analysis we consider the time interval of 16-56 month as the period when the primary outcome of live birth accumulates. Realistically though, only interim looks prior to month 40 of the trial will affect future recruitment while looks between 40 and 56 months can only affect decisions regarding continuing active or passive follow-up of subjects already enrolled in the trial.

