The following Tables 3 and 4 present results of power calculations for various interim looks plans for the EAGeR trial. These demonstrate the implications of different choices for the number and timing of interim looks. We assume throughout an alpha level of 0.05 and a sample size of 1600 women divided equally to the aspirin and placebo arms of the trial. Previously published studies suggest that for the control group a probability of about 0.70 - 0.80 for live birth given pregnancy ( $P_{preg}$ ) can be expected. Further, the probability of implantation per cycle ( $P_{implant}$ ) was assumed to be constant and in the range between 0.175 and 0.25. Figure 4 shows the probability of live birth (PLB) considering six cycles of menstruation (including both active and passive follow-up):

$$PLB = P_{preg} P_{implant} \sum_{c=1}^6 (1 - P_{implant})^{c-1}$$

**Figure 4.** Probability of live birth versus implantation probability per menstrual cycle

[figure not shown]

Hence a conservative estimate for the live birth rate would be a combination of implantation rate or 17.5% per cycle and a probability of live birth given pregnancy of 70% yielding an estimated value of  $PLB = 0.479$ . The final calculations will be done after the population from which participants are drawn will be identified. A refinement of the calculation can easily incorporate non-fixed probabilities of implantation per cycle

In the following, we consider a range of probabilities for the placebo + folic acid arm of 0.46, 0.48 and 0.50. The effect of the intervention will be measured as the rate ratio (RR) of live birth in the aspirin + folic acid arm compared to placebo + folic acid. We consider effect sizes of 1.15, 1.20 and 1.25. The calculations were preformed using PASS software. Table 3 presents the resulting power for no interim looks and Table 4 shows the power for one or two interim looks for selected outcome probabilities and effect size.

**Table 3.** Power for comparing live birth rates in treatment and placebo groups with no interim looks.

| Live Birth Probability in placebo arm | Live Birth Rate Ratio to be Detected |            |      |
|---------------------------------------|--------------------------------------|------------|------|
|                                       | 1.15                                 | 1.20       | 1.25 |
| 0.46                                  | .77                                  | .96        | .99  |

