| 0.48                                  | .81                                  | .97 | 1.0  |
| 0.50                                  | .84                                  | .98        | 1.0  |

Table 3 shows for example that with 800 women in each treatment arm, we have >80% power to detect effects  $\geq 1.15$  for an assumed overall live birth rate of 0.48 in the placebo group.

Table 4 gives the power for one or two interim looks and the Z-score boundaries, assuming PLB = 0.48 in the placebo arm and a rate ratio of 1.20. For the period 16 – 56 months when live births accumulate, an interim look at 0.45 and 0.6 of the way correspond to 18 and 24 months into the planned recruitment period. In other words, stopping at month 18 of recruitment (24th month of the trial) will “save” the last 6 months of recruitment while by 24 months of recruitment (30th month of the trial) the target sample size should be reached and the stopping will apply to cessation of follow-up and data collection. Alternatively if at this stage aspirin is shown to be effective one could switch the placebo patients to aspirin and continue the follow-up. The decision to stop early will not be made solely on the basis of these statistical tests but will be made by the DSMB taking into account all available information including evaluation of secondary outcomes and ethical issues.

**Table 4.** Power for one or two interim looks assuming PLB = 0.48, RR = 1.2

| Number of interim looks | Time of interim looks | Boundaries  | Power |
|-------------------------|-----------------------|-------------|-------|
| 1                       | 0.45                  | $\pm 2.571$ | 0.490 |
|                         | 1.00                  | $\pm 2.010$ | 0.964 |
| 1                       | 0.60                  | $\pm 2.366$ | 0.718 |
|                         | 1.00                  | $\pm 2.038$ | 0.963 |
| 2                       | 0.45                  | $\pm 2.571$ | 0.490 |
|                         | 0.60                  | $\pm 2.485$ | 0.696 |
|                         | 1.00                  | $\pm 2.050$ | 0.962 |

Thus for example, compared to the naive power of 0.97, one interim look at 0.45 of events accumulation period will results in a very small loss of total power to 0.964

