## Interim Analysis

### 1.1 Preliminaries

#### 1.1.1 Sample size, proportions, and the test statistic

Let  $N = N_0 + N_1$  be the trial total sample size, where  $N_0$  is the sample size in the placebo group and  $N_1$  is the sample size in the treatment group. Let  $n_0, n_1$  be the number of completed participants at the time of the interim analysis, in the placebo and treatment groups respectively. Completed participant include all sort of completion except for withdrawal. In the following calculations we assume that  $n_0 = n_1$ , and define  $n = n_0 + n_1$ . In particular, we use the notation  $t = n/N$  in order to express the time  $t$ .

Let  $p_0$  be the proportion of live birth in the placebo group under  $H_0$ , and  $p_1$  be the proportion of live birth in the treatment group under  $H_1$ . Let  $\hat{p}_0(t)$ , and  $\hat{p}_1(t)$  be the observed proportions of live birth in the placebo and treatment groups at time  $t$  respectively. We denote the difference between the proportions by  $\delta = p_1 - p_0$ , and its estimator by  $\hat{\delta}(t) = \hat{p}_1(t) - \hat{p}_0(t)$ . Thus, if  $n_0 = n_1$ , we can use the identity  $t = n/N$ , and define the test statistic to be

$$Z(t) = \sqrt{t} \frac{\hat{\delta}(t) \sqrt{N}}{2\sigma}, \quad (1.1)$$

where

$$\sigma = \sqrt{\frac{p_1(1-p_1)}{2} + \frac{p_0(1-p_0)}{2}}. \quad (1.2)$$

Group sequential procedures for interim analysis are based on their equivalence to discrete boundary crossing of a Brownian motion process with drift parameter  $\theta$ . The test statistics  $Z(t)$  follow the multivariate normal distribution with means  $\sqrt{t}\theta$  and, for  $t_1 < t_2$ , covariances  $\sqrt{t_1/t_2}$ . The drift parameter  $\theta$  is related to the parameters of the z-test through the equation

$$\theta = \frac{\delta \sqrt{N}}{2\sigma}. \quad (1.3)$$

We note that  $\theta$  is independent of  $t$  and is pre-specified in the beginning of the trial.

In the sequel we consider the following scenarios. The total sample size is  $N = 1600$ , where  $N_1 = N_0 = 800$ . For the placebo proportion we consider the values  $p_0 = 0.4, 0.42, 0.44, 0.46, 0.48$ . The treatment proportions will be calculated as  $p_1 = RR * p_0$ , where  $RR$  is the relative risk according to the EAGeR protocol. Specifically, we consider  $RR = 1.15, 1.2, 1.25$ .

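### Alpha is spent on elapsed time in the protocol but on the share of completed participants in the interim chapter, and nothing says which governs, so the efficacy stopping threshold is undefined

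*Supplement*

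**What the plan says.** Protocol G.3 adopts Lan-DeMets spending: "For the EAGeR trial the spending function corresponding to the O'Brien-Fleming procedure will be used". It then fixes the time scale: "For our implementation the rate at which Type I error is spent is a function of elapsed time". The window follows: "we consider the time interval of 16-56 month as the period when the primary outcome of live birth accumulates". The fraction at month m is therefore (m - 16)/40. Table 4 labels its looks 0.45 and 0.60 and gives boundaries and power at those fractions.

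The interim analysis chapter (section 1.1.1) uses another scale. It sets t = n/N with N = 1600, where n sums what are defined to "be the number of completed participants at the time of the interim analysis, in the placebo and treatment groups respectively", and "Completed participant include all sort of completion except for withdrawal". Section 1.1.2 computes efficacy boundaries from a spending function on that t (equation 1.4) and attributes this to the protocol. The chapter does not mention elapsed time, and neither document maps one scale to the other or says that one replaces the other.

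**The concern.** A spending function gives a boundary only once its time argument is fixed. Here two arguments stand for one alpha(t), and the chapter that changes the argument says it follows the protocol. An analyst preparing an efficacy look for the DSMB would have to choose, and the choice moves the threshold and the chance of stopping early.

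Lan-DeMets designs may use two times: one for spending alpha, and one, the information fraction, for the correlation between looks. The plan does not draw this distinction. Table 4 uses the calendar fraction for both, so its interim power describes data that are 45% or 60% complete, whatever has accrued by that date.

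**Working it through.** **Inputs from the documents.** G.3: "We assume throughout an alpha level of 0.05 and a sample size of 1600 women divided equally to the aspirin and placebo arms"; G2.2: a "two-sided test based on the standard Z-score"; window 16-56; looks at 0.45 and 0.60; p0 = 0.48 and rate ratio 1.20; implantation 0.175-0.25 per cycle for six cycles; live birth given pregnancy 0.70-0.80.

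**Assumed, because the documents do not give n/N.** Uniform accrual from month 6 to 40, 28-day cycles, birth about 35 weeks after the positive test, close-out lag 0-2 months, no withdrawals.

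**Step 1: reproduce the plan.** PLB = 0.70 × (1 - 0.825^6) = 0.479, as stated. The chapter's drift values 3.864 and 2.43 and powers of 97% and 68% also reproduce. Table 4's boundaries do not. O'Brien-Fleming-type spending totalling 0.05 is α(t) = 4 - 4Φ(2.2414/√t).

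- At t = 0.45: 2.2414/0.6708 = 3.341; α = 0.001668; half per tail gives z = 3.144. Table 4 prints 2.571.
- At t = 0.60 the result is 2.669. Table 4 prints 2.366.
- With both looks the function gives 3.144, 2.693 and 1.982. Table 4 prints 2.571, 2.485 and 2.050.
- The printed values match α(t) = 0.05t². For example, 0.05 × 0.45² = 0.010125 gives z = 2.572, and both looks give 2.572, 2.485 and 2.047. With this spending, a continuity correction, and 0.45 and 0.60 taken as information, power is 0.490, 0.695 and 0.962 (Table 4: 0.490, 0.696 and 0.962).

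Equation 1.4 as printed has 2 - 2Φ, which totals 0.025 at t = 1 although the text sets 0.05. I use the doubled form. Taken literally, 1.4 gives 3.341 at 0.45.

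**Step 2: compare the scales (first look at each month).**

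| Month | Calendar t | z | n/N | z |
|---|---|---|---|---|
| 24 | 8/40 = 0.20 | 4.88 | 0.24-0.30 | 4.41-3.92 |
| 30 | 14/40 = 0.35 | 3.61 | 0.42-0.48 | 3.27-3.04 |
| 34 | 18/40 = 0.45 | 3.14 | 0.54-0.59 | 2.85-2.68 |
| 40 | 24/40 = 0.60 | 2.67 | 0.71-0.77 | 2.41-2.30 |

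Other cycle lengths and closing times widen month 34 to about 0.52-0.60, which gives z = 2.90 to 2.67. Months 24 and 30 are shown because G.3 says "an interim look at 0.45 and 0.6 of the way correspond to 18 and 24 months into the planned recruitment period" and equates these with trial months 24 and 30. On its own window, 0.45 and 0.60 are months 34 and 40.

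With two looks at months 34 and 40, the calendar scale gives 3.14, 2.69 and 1.98. The n/N scale (0.59 and 0.76) gives 2.70, 2.36 and 2.02.

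**Step 3: operating characteristics.** One look at month 34 with n/N = 0.594 and rate ratio 1.2:

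- Calendar spending with n/N correlations: 3.144 then 1.962, and a 42% chance of crossing at the look.
- n/N spending: 2.684 then 1.980, and a 60% chance.
- Each rule fixed in advance has type I error 0.050. Rejecting when either is crossed gives 0.0507 (look at month 30), 0.0520 (month 34) or 0.0548 (month 40).

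**Step 4: who is completed early (a separate point).** Losses and non-pregnancies close sooner than births. With losses assumed to close 0.5-2.5 months after the positive test, implantation 0.175 and live birth given pregnancy 0.70, the live-birth proportion among completed women is about 0.34 at month 24 and 0.41 at month 34, against 0.48 eventually.

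**The case against.** The strongest reply is that the chapter is a later operational definition of t, written mainly for futility. Its worked cases have no efficacy look and use a final critical value of 1.96, so Table 4 holds the only printed efficacy boundaries. This stands in part: the documents do not contain two rival sets of published boundaries, though a reader might infer that they do. But section 1.1.2 still prescribes efficacy boundaries on n/N, and no text withdraws the elapsed-time rule.

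Four stronger readings are tempting, and the documents do not support them.

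- **That calendar-time spending is invalid.** It is valid if fixed in advance, with true information used for the correlations.
- **That type I error is lost.** It is held at 0.05 under either rule; the small excess needs a choice made after seeing data.
- **That a given Z, say 2.9 at month 34, would stop the trial under one document and not the other.** It exceeds Table 4's printed 2.571 and, at n/N = 0.52, clears the n/N boundary (2.897) by only 0.003. Under equation 1.4 read literally it crosses neither scale at n/N = 0.59 (3.341 and 2.918). G.3 also leaves stopping to the DSMB's wider judgement.
- **That leaving withdrawals out of n is an error of the clock.** G.1 defines the 1600 as completers without dropouts, so numerator and denominator agree.

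The enrichment in Step 4 concerns who enters the interim comparison, not which scale spends alpha, and under the null it affects both arms alike.

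**Conclusion.** The contradiction is in the text and does not depend on any assumption. Its size does: the n/N figures rest on assumed accrual and completion timing, and the boundaries on O'Brien-Fleming-type spending totalling two-sided 0.05. n/N led the calendar fraction in every scenario tried. If the target were reached by month 30, as G.3 suggests, the gap at that month would be wider: 3.61 against 2.69-2.49. Under 0.05t² spending the month-34 gap is smaller: 2.57 against about 2.37-2.47.

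The consequence is an undefined efficacy threshold and a materially different chance of early stopping. It is not a broken type I error rate. Table 4 cannot settle the matter, because it equates calendar fraction with information and its boundaries do not follow the stated function on either scale. This should be corrected before any efficacy look.

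**What to change.** 1. State one pre-specified spending scale in G.3 and in the interim chapter. Elapsed time and n/N are both acceptable.
2. State separately the information fraction used for the correlations. Base it on the women actually in the interim comparison, with numerator and denominator defined alike.
3. Recompute Table 4's boundaries and power from the stated spending function, and write equation 1.4 so that it totals the intended alpha.

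This costs wording in two places and one computation.

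Separately, the sponsor could restrict each look to women whose full follow-up window has closed, which would remove the enrichment for losses and non-pregnancies. That is not a small cost: on the assumed timings, the usable fraction at month 34 falls from about 0.55-0.60 to about 0.38-0.43. If this is adopted, the plan should state that loss.

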## **G. STATISTICAL ANALYSIS**

### **G.1 Overview**

The EAGeR trial is designed as a multi-site randomized double blind clinical trial with two treatment arms: folic acid + aspirin compared to folic acid + placebo. A fixed sample size of 1600 randomized complete subjects is planned. Thus, for planning and statistical power computations we assume that this is the number of subjects who complete the trial and does not include dropouts.

The primary analysis plan is based on an “intention-to-treat” approach comparing the two treatment arms based on the randomized assignment, ignoring later changes in treatment. This analysis is described in Section G.2. The Haifa DCC will perform periodic partial analyses and present interim reports to the DSMB as requested, during Phase II of the trial. It is anticipated that partial analyses will be performed every 6-12 months. The final analysis will be performed upon completion of data collection and editing in Phase III of the trial. Also one full formal interim analysis is planned and the power calculations with considerations for the choice of optimal time for the analysis are given in Section G.3.

In addition to the intention to treat analysis, the Haifa DCC will engage in methodological research with the Project Officer at the NICHD. The focus is on developing statistical methods for clinical prediction models of reproductive outcomes as described in Section G.4, analysis of intermediate endpoints (Section G.5) and evaluating the effect of dropouts and compliance on the study results (Section G.6).

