Even with two interim looks there is very little power loss. Two interim looks at 18 and 24 months into the planned recruitment period yield a high total power of 0.962 and is the proposed plan for the trial.

The high power shown for assessing an effect size of RR =1.2 for the primary outcome of the EAGeR trial indicate that more modest effects could be detected with high probability.

The Lan-DeMets methodology is flexible in that the total number and timing of the interim looks does not need to be specified in advance. Based on results of periodic partial analyses additional looks can be planned and the test boundaries can be adjusted according to the spending function.

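### G.3 dates its two interim looks to trial months 24 and 30, but the fractions 0.45 and 0.60 behind Table 4 fall at months 34 and 40 on its own clock, and G.1 plans only one look

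*Supplement*

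**What the plan says.** G.3 makes alpha spending a function of elapsed time and fixes the window: "for the interim analysis we consider the time interval of 16-56 month as the period when the primary outcome of live birth accumulates". The same paragraph gives the recruitment calendar: "The accrual period will continue through month 40 while Phase II ends by month 57". Table 2 agrees, with recruitment in months 7 to 40.

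After Table 3, G.3 says that "an interim look at 0.45 and 0.6 of the way correspond to 18 and 24 months into the planned recruitment period". It equates these dates with trial months 24 and 30. It adds that stopping at the first look would save the last six months of recruitment, and that by the second look "the target sample size should be reached and the stopping will apply to cessation of follow-up and data collection". Table 4 then gives the two-look design at fractions 0.45, 0.60 and 1.00: boundaries ±2.571, ±2.485 and ±2.050, with cumulative power 0.490, 0.696 and 0.962. G.3 adopts this as the proposed plan: "Two interim looks at 18 and 24 months into the planned recruitment period yield a high total power of 0.962".

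On the number of looks, G.1 says: "Also one full formal interim analysis is planned".

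The separate Interim Analysis chapter defines t as n/N, the share of participants who have completed. It gives no calendar dates. Its sensitivity calculations assume one futility look and no efficacy look.

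**The concern.** Eighteen and 24 months are 0.45 and 0.60 of a 40-month span, but that span begins at month 16, when the first births are expected. G.3 counts the 18 and 24 months from the start of recruitment, at about month 6, so its dates are ten months too early for the fractions it uses.

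The adopted dates and the quoted operating characteristics thus belong to different designs. A monitoring board meeting at months 24 and 30 would have less information than Table 4 assumes and a much smaller chance of stopping early for benefit. If the board took month 24 to be fraction 0.45, as the text says, it would also spend alpha faster than the plan allows. And it could not tell from the protocol whether one or two formal looks were intended.

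**Working it through.** **Inputs.** "We assume throughout an alpha level of 0.05 and a sample size of 1600 women divided equally to the aspirin and placebo arms" (G.3). The test is a "two-sided test based on the standard Z-score" (G2.2). Table 4 takes live-birth probabilities of 0.48 and 0.48 × 1.20 = 0.576. The clock runs over months 16 to 56, so 40 months.

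**1. Dates against fractions.** Month = 16 + 40f, and f = (month − 16)/40.

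| | First look | Second look |
|---|---|---|
| Fraction used in Table 4 | 0.45 | 0.60 |
| Month for that fraction | 16 + 18 = 34 | 16 + 24 = 40 |
| Month stated in G.3 | 24 | 30 |
| Fraction at the stated month | 8/40 = 0.20 | 14/40 = 0.35 |

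**2. Stated consequences against the accrual calendar.** With accrual to month 40, stopping at month 24 leaves 16 months of recruitment unspent, not 6, and at month 30 ten months remain. G.3's statements fit a 24-month recruitment period (24 − 18 = 6 months saved; target reached at month 6 + 24 = 30). They would also fit looks at months 34 and 40 under accrual to month 40. Neither reading makes the stated dates, the fractions and the accrual end agree.

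**3. Reproducing Table 4.** Drift θ = δ√N/(2σ), with δ = 0.096 and σ² the mean of the two binomial variances. This gives θ = 3.864 unpooled, or 3.846 pooled. Boundary-crossing probabilities were found by numerical integration. With spending α·t² at 0.45, 0.60 and 1.00:

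- boundaries 2.572, 2.485 and 2.047 (Table 4: 2.571, 2.485, 2.050);
- cumulative power 0.503, 0.709 and 0.966, pooled (Table 4: 0.490, 0.696, 0.962).

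So Table 4 was computed at 0.45 and 0.60. It does not match the O'Brien-Fleming-type spending that G.3 names: 4 − 4Φ(z₁₋α/₄/√t) at the same fractions gives boundaries 3.144, 2.693 and 1.982 with power 0.29, 0.62 and 0.97. Any comparison across dates must therefore hold the spending function fixed.

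**4. Operating characteristics at the stated dates (0.20, 0.35, 1.00).**

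| Boundaries | Values | Two-sided type I error | Cumulative power |
|---|---|---|---|
| Table 4, unchanged | 2.571, 2.485, 2.050 | 0.0552 | 0.20, 0.44, 0.97 |
| Recomputed, α·t² | 3.09, 2.82, 1.99 | 0.050 | 0.09, 0.31, 0.97 |
| Recomputed, O'Brien-Fleming type | 4.88, 3.61, 1.96 | 0.050 | 0.001, 0.09, 0.97 |

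At 0.45 and 0.60, Table 4's boundaries give an error of 0.0497, so the excess comes from the dates.

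**5. Would the n/N clock rescue the dates?** The documents give no accrual curve or completion lag for it. Assume even accrual from month 6 over 34 months and a common lag of 6 to 15 months from randomization to completion; n/N is then (month − 6 − lag)/34. Month 24 gives 3/34 to 12/34, or 0.09 to 0.35. Month 30 gives 9/34 to 18/34, or 0.26 to 0.53. Both fall short of 0.45 and 0.60. With 24 months of accrual the ranges become 3/24 to 12/24 (0.13 to 0.50) and 9/24 to 18/24 (0.38 to 0.75), so the tabled fractions could be met, but only on a recruitment plan that contradicts Table 2.

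**The case against.** The strongest reply is that Lan-DeMets spending exists to absorb this kind of slip. G.3 says that the number and timing of looks need not be fixed in advance and that boundaries can be adjusted by the spending function. It presents Tables 3 and 4 as illustrations of different choices. The Interim Analysis chapter measures time by completed participants, so calendar months do not set t there. Final power is intact, and G.3 does not let the statistical tests alone decide whether to stop.

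Most of this stands, and it limits the harm. A reader might infer that the plan as a whole fails to hold the 5% error. The documents do not support that: the 0.055 needs Table 4's cut-offs to be applied unchanged at months 24 and 30, and boundaries recomputed at the true fraction hold the error.

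A reader might also infer that looks at these dates could hardly ever stop the trial. That is so at both looks under O'Brien-Fleming-type spending (0.001, then 0.09). Under the spending that reproduces Table 4, the chance of having stopped by the second look is about 0.31. Setting Table 4's 0.490 and 0.696 beside the O'Brien-Fleming figures mixes two spending functions.

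What does not stand is that flexibility removes the problem. Adjusting boundaries requires the right fraction at the look, and G.3 tells the board that month 24 is 0.45. The Interim Analysis chapter supplies neither dates nor a settled number of looks.

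**Conclusion.** The inconsistency is established from G.3 alone. The stated dates are ten months earlier than the fractions used for Table 4, the implied recruitment length conflicts with G.3's own accrual end and Table 2, and G.1 and G.3 disagree on the number of formal looks.

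The main effect is on early stopping. The quoted 0.490 and 0.696 do not apply at months 24 and 30; like for like they become about 0.09 and 0.31. Type I error is affected only conditionally, by about half a percentage point, and final power hardly at all. These figures assume G.3's elapsed-time clock, treated as the information fraction, with 800 women per arm and rates of 0.48 and 0.576.

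It is tempting to conclude that months 34 and 40 were the intended dates. The documents do not show this, because G.3's wording is equally consistent with a 24-month recruitment plan. The passages need to be reconciled, and it should be done before the first look, because they govern when and at what threshold the trial could stop for benefit.

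**What to change.** Bring G.1, G.3, Table 2 and the Interim Analysis chapter to one number of formal looks, one clock (elapsed time or n/N completed) and one set of dates. There are two coherent routes:

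- **Keep 0.45 and 0.60.** State the looks as trial months 34 and 40, and correct the sentences on months 24 and 30. Note that, by G.3's own reasoning, a look at month 40 can no longer affect recruitment. The cost is a later first look.
- **Keep months 24 and 30.** Restate boundaries and stopping power at the fractions those dates deliver (0.20 and 0.35 on the elapsed-time clock), and correct the statements about recruitment saved and target reached. The cost is much less favourable stated early-stopping power.

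On either route, compute the boundaries from the spending function the protocol names, at the actual fraction at each look, and replace Table 4 accordingly. The work is limited to protocol wording, one recomputed table and the monitoring board's calendar. Sample size and final power need not change.
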